# The impact of electronic cigarettes on pregnancy and childhood health outcomes: the ECHO study—a protocol for a multicentre, prospective, observational, cohort

**DOI:** 10.1007/s00404-025-08066-8

**Published:** 2025-06-20

**Keywords:** Vaping, Smoking cessation in pregnancy, Preterm birth

## Abstract

**Background:**

Stopping cigarette smoking in pregnancy positively impacts on the incidence of preterm birth, intrauterine growth restriction, and stillbirth. Electronic cigarettes (E-cigarettes) are viewed by some women as a lower risk alternative to tobacco smoking during pregnancy and are cautiously endorsed in some parts of the UK to support smoking cessation(1), however, robust, high-quality data on the impact of E-cigarettes on pregnancy and childhood health outcomes are lacking.

**Objective:**

The objective of the ECHO study is to investigate the impact of maternal E-cigarette use during pregnancy on obstetric, neonatal, and infant outcomes.

**Methods:**

Pregnant women attending three, large, standalone, urban, university, maternity units in Dublin, Ireland, will be invited to take part in this prospective, multicentre, observational cohort. Smoking and vaping patterns will be assessed using digital patient questionnaires. Objective assessment of breath carbon monoxide and urine cotinine levels will accurately determine exposure status at pre-specified timepoints. A third trimester ultrasound will assess growth and fetal dopplers across all groups. Postnatally, infants will undergo anthropometric measurements and developmental checks. A subgroup of 150 randomly selected infants will be assessed with the Bayley’s Scales of Infant and Toddler Development.

**Discussion:**

Nicotine-containing E-cigarettes are addictive and their long-term impact on pulmonary, cardiovascular, and neurological function on developing humans is undetermined. This study is ambitious as it aims to longitudinally assess the outcomes of the mother/baby dyad, examining the impact of vaping on pregnancy, neonatal and infant health, growth and neurocognitive outcomes.

**Trial registration:**

ClincialTrials.gov NCT06297005

## Background

Combustible cigarette smoking is the foremost modifiable risk factor for adverse pregnancy outcomes [2]; therefore, encouraging women to stop smoking in pregnancy is a key public health priority [3]. Combustible cigarette smoking during pregnancy is associated with an increased risk of fetal anomaly [4], small for gestational age and stillbirth, preterm birth, low birth weight [5], placental abruption, sudden infant death syndrome [6], respiratory morbidity in the neonatal period [7], asthma and longer term neurodevelopmental delay [8]. Increasingly, it is accepted that intrauterine growth and development are strong determinants of health, not only in the neonatal period, but also impact on childhood and adult health outcomes [9, 10]. Pregnancy can be a motivator for smoking cessation, with quit attempts higher than at any other time in a woman’s life [11]; smoking cessation prior to or during the first trimester of pregnancy significantly reduces the risk of preterm birth [8] and impacts positively on birthweight [12].

Nicotine replacement therapy (NRT) in the form of patches, inhalers, lozenges etc., has been prescribed for pregnant women seeking pharmacological support to stop smoking for decades; it accepted to be significantly less harmful to the fetus than continuing to smoke combustible tobacco cigarettes [13, 14].

Electronic cigarettes (E-cigarettes) or ‘vapes’ are viewed as a reasonable alternative to combustible cigarette smoking by some women and are now endorsed by some health policy makers in the United Kingdom to support women to stop cigarette smoking in pregnancy [15]. However, there is a paucity of high-quality, prospective data assessing the impact of electronic cigarettes on pregnancy, neonatal, and infant outcomes. In the following protocol, registered with ClincialTrials.gov (NCT06297005), we outline a multicentre, prospective, observational cohort study of pregnancies exposed to vaping to address this research gap.

### Why is combustible cigarette smoking cessation during pregnancy so important for adverse birth outcomes?

Globally, preterm birth is the leading cause of neonatal morbidity and mortality [16]; in addition to the significant personal toll, the economic impact of preterm birth cannot be overstated [17]. Complete combustible cigarette smoking cessation during pregnancy could reduce preterm birth rates in high-income countries by 5–8% for extreme preterm birth (<32 weeks), 3–4% of preterm births (<37 weeks), and crucially a 5–7% reduction in stillbirth [18, 19]. Supporting smoking cessation during pregnancy can positively impact maternal, fetal, infant, child, and therefore overall population health in the longer term; however, the optimum means to facilitate smoking cessation in pregnancy is undetermined [12] and there are high rates of relapse in the puerperium.

### Nicotine and nicotine replacement therapy

Nicotine is a naturally occurring alkaloid and the addictive component of tobacco and nicotine-containing vape products. Although previous publications advised of the teratogenic potential of nicotine, [20] their conclusions are largely extrapolated from studies of pregnant combustible cigarette smokers or from exposed animal models [7, 21]. A recent, large, multi-national, retrospective, cohort study robustly demonstrated that there was no increased risk of major congenital malformation in women using NRT in the 90 days prior to and during pregnancy [14]. The compelling question remains regarding the issue of neurocognitive impact in infants of mothers exposed to nicotine: evidence here is sparse.

During pregnancy, nicotine metabolism is enhanced in comparison to the non-pregnant population [22]. The effectiveness of NRT in assisting cigarette smokers to stop smoking has not been replicated in the pregnant population. This is potentially due to sub-therapeutic dosing levels related both to the quitter’s concerns about nicotine exposure [23] and the prescribers’ lack of training [24]. Nicotine readily crosses the placental barrier and there is evidence of accumulation of nicotine in fetal serum and amniotic fluid in higher concentrations than in maternal serum [25]. In addition, neonates demonstrate a diminished ability to metabolise nicotine, resulting in a half-life of three to four times that of an adult for second-hand smoke [2]. NRT, although not first line, is conservatively endorsed internationally to aid supporting women to stop cigarette smoking in pregnancy [26]. Whilst there is no robust evidence to state that NRT causes significant harm during human pregnancies [13, 14], its effectiveness for smoking cessation in this cohort is mixed [27].

### Electronic cigarettes/vapes

Electronic cigarettes, colloquially known as ‘vapes’, are battery powered devices that heat a solution (e-liquid) to create a nicotine-containing aerosol. In addition, the e-liquid often contains different flavourings, as well as the compounds propylene glycol and glycerine. The evaporation of the liquid at the heating element is followed by rapid cooling to form an aerosol which is directly inhaled (or “vaped”) by the user through a mouthpiece. Each device includes a battery, a reservoir that contains the liquid, and a vaporisation chamber with a heating element [28]. The newest generation E-cigarette devices facilitate blood serum nicotine concentrations that are equivalent to that of a traditional combustible cigarette [29]; the method of use is similar to conventional combustible cigarettes resulting in an experience for the user that is closer to cigarette smoking than any other forms of NRT, and likely explains the growing popularity of vapes as a smoking cessation tool [30]. Importantly, vaping does not generate carbon monoxide, the primary, deleterious by-product of combustible cigarette smoking.

### Note on nomenclature

Electronic cigarette users will be identified as ‘vapers’ throughout the manuscript; combustible cigarette smokers as ‘smokers’; and women who use neither electronic nor combustible cigarettes will be identified as controls.

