## Objectives

The ECHO study has four primary objectives described below:The primary obstetric objective is to establish whether infants born to women who vape are at a higher or lower risk of adverse outcomes in pregnancy compared to infants of combustible cigarette smokers and non-smokers.The primary neonatal objective is to assess anthropomorphic variation, if any, in newborn babies born to vapers in comparison to smokers and controls. The primary paediatric objective is to establish whether parent-reported and doctor-confirmed wheeze and/or asthma occurs more frequently in children exposed to vaping in utero compared with children of combustible cigarette smokers and non-smokers.The primary neurocognitive objective is to assess if there are significant differences in neurocognitive outcomes between the infants of a women who vape compared to infants of women who used combustible cigarette smokers and non-smokers.Globally, we aim to correlate, obstetric, neonatal, pulmonary, growth and neurocognitive differences, if any, to quantitative levels of cotinine excreted in maternal urine at in the third trimester.

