### Population

This prospective, multicentre, observational cohort will focus on women pregnant with a singleton fetus who self-report vaping, cigarette smoking, vaping and cigarettes smoking, or no exposure (controls). The obstetric portion of the study operates from three recruitment sites; The Coombe Hospital, The Rotunda Hospital, and the National Maternity Hospital—these standalone maternity units, based in Dublin, Ireland’s capital city, cumulatively deliver approximately 22,000 women annually [31–34].

Smoking and vaping patterns will be assessed using a combination of digital validated patient questionnaires administered at set timepoints throughout pregnancy, in addition to objective assessment of exhaled breath carbon monoxide (BCO) assessed by point of care exhaled carbon monoxide breathalysers (Bedfont’s ‘Smokerlyzer’® device) at each antenatal study visit. Nicotine levels will be assessed using quantitative urinary cotinine, analysed by Eurofins Biomnis enzyme immunoassay.

Women are recruited prior to 24-week gestation after being directly asked about smoking and vaping status in a structured fashion at their booking visit; if they fulfil the eligibility criteria, they are then invited to partake in the study as either a vaper, a smoker, a smoker/vaper or a control (Table 1.).

**Table 1 Tab1:** Exposure status

Vaper	Vaper/smoker	Smoker	Control
• Reports vape use • BCO ≤4 ppm	• Reports dual use • BCO ≥ 5 ppm	• Reports cigarette smoking • BCO ≥ 5 ppm	• Denies cigarette smoking or vaping • BCO ≤4 ppm

A BCO measurement of ≥ 5 parts per million (ppm) was selected to define active smoking, in keeping with Irish National Clinical Guidance. Selection of BCO ≥ 5 ppm as a cutoff confers a sensitivity of 0.9 and specificity of 0.92 [35]. This is an important consideration in accurately classifying both smokers and smoker/vapers in addition to self-reported exposure status.

After screening, demographic and biometric data points are gathered, and a series of questionnaires are administered digitally as per the schedule outlined below:

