### Inclusion criteria

Women aged 18 or greater and less than 46 years of age at booking.Pregnant with a singleton fetus.Smoker or vaper or smoker/vaper or control.Able to understand and read English.Willing to agree to follow-up for the 2-year duration of the study in the postnatal period

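### The control definition lets women using only nicotine replacement therapy into a group labelled unexposed; a minor flaw that is cheap to close

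*Protocol article*

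**What the plan says.** The protocol article fixes who is a control in two places. The Note on nomenclature states that "women who use neither electronic nor combustible cigarettes will be identified as controls". The control column of Table 1 (Population section) reads "Denies cigarette smoking or vaping • BCO ≤4 ppm". The Inclusion criteria list only four categories, "Smoker or vaper or smoker/vaper or control", with no condition on other nicotine products, and the Exclusion criteria do not mention NRT.

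The Population section describes the groups as including "vaping and cigarettes smoking, or no exposure (controls", so controls are presented as unexposed. The abstract says that BCO and urine cotinine together will determine exposure status, but no cotinine criterion appears in Table 1. Cotinine is sampled in the third trimester (Exposure section), whereas recruitment takes place before 24 weeks.

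On NRT, the Background says that it "has been prescribed for pregnant women seeking pharmacological support to stop smoking for decades", and the section on nicotine and NRT says "NRT, although not first line, is conservatively endorsed internationally". That section also says that nicotine crosses the placenta and that its neurocognitive effect on infants is an open question. One overall aim is to relate outcome differences to "quantitative levels of cotinine excreted in maternal urine".

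**The concern.** A woman who has stopped smoking and uses patches, lozenges or an inhaler can truthfully deny smoking and vaping and can have a BCO of 4 ppm or less. She satisfies every printed control criterion, yet her pregnancy is exposed to nicotine and she has probably smoked recently. BCO cannot pick her out: the article chose its cut-off to define active smoking and describes carbon monoxide as a product of combustion. For the same reason BCO cannot reveal a woman who vapes and does not say so.

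The first hypothesis compares vapers with non-smokers. If some of the reference group carry raised risk from nicotine or recent smoking, that contrast is diluted towards no difference, and so is the smoker-control contrast. The planned power at 400 per group is about 80%, with no reserve. The point matters most for the neurocognitive outcomes, where the article itself treats the effect of nicotine as unresolved.

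**Working it through.** **1. Can an NRT-only user be a control?** Taking each printed rule in turn:

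- Nomenclature note: uses neither electronic nor combustible cigarettes. Met.
- Table 1: "Denies cigarette smoking or vaping". Met.
- Table 1: BCO at most 4 ppm. Can be met, since NRT involves no combustion.
- Inclusion and exclusion criteria: no NRT condition. Met.
- Cotinine: not part of the group definition, and taken after enrolment. The article gives a half-life of 19 hours and describes cotinine as reflecting use over days, so a third-trimester sample would miss NRT used early and then stopped.

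No printed rule excludes her.

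**2. Reproducing the plan's figures.** Inputs from the power section: 400 per group, 80% power, type I error 0.05 (taken as two-sided), uncorrected chi-square test. With pooled variance,

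power = Φ{ [ |p2 − p1|·√n − 1.96·√(2·p̄(1 − p̄)) ] / √( p1(1 − p1) + p2(1 − p2) ) }.

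The detectable odds ratio (OR) is 1.81 for wheeze at a 10% baseline (Table 3: 1.80) and 2.04 for preterm birth at 6.2% (Table 3: 2.04). Both reproduce.

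**3. Dilution, wheeze.** Baseline 10%, OR 1.8. Exposed odds = 1.8 × 0.10/0.90 = 0.20, so p2 = 0.20/1.20 = 0.1667. Let a share f of controls be NRT users and, as a worst case, give them the full exposed risk. The control risk is then (1 − f) × 0.10 + f × 0.1667.

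- f = 0: power = Φ[(1.333 − 0.942)/0.478] = Φ(0.817) = 79.3%.
- f = 2% (8 of 400): control risk 0.1013, odds 0.1128, OR = 0.20/0.1128 = 1.77. Power = Φ[(1.307 − 0.944)/0.480] = Φ(0.756) = 77.5%.
- f = 5%: OR 1.74, power 74.7%.
- f = 10%: OR 1.675, power 69.6%.

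For preterm birth at OR 2.04, a 2% share gives OR 2.00 and moves power from 80.1% to 78.3%.

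**4. Which f is credible?** The article gives no NRT share, so f is an assumption. Its prevalence figures give a rough check. Of about 22,000 births, 10% smoking is 2,200 and 5% vaping is 1,100. With no overlap, 22,000 − 2,200 − 1,100 = 18,700 use neither. If controls are drawn from that pool:

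- f = 2% means 374 abstinent NRT users, 17% as many as all current smokers (374/2,200).
- f = 5% means 935, or 42%.
- f = 10% means 1,870, or 85%.

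The two larger shares are hard to reconcile with the article's statement that the effectiveness of NRT for stopping smoking has not been replicated in pregnancy.

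**The case against.** The strongest reply is that the exposure of interest is e-cigarette use. An NRT-only user is unexposed to both vaping and smoking, and the objectives and hypotheses name non-smokers, not nicotine-free women, as the comparator. That stands, and it limits the point: she is not misclassified with respect to vaping. It does not remove the mismatch between the printed rule and the description of controls as unexposed.

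Second, dilution is conditional. The article reports no robust evidence that NRT causes significant harm in human pregnancy and regards it as much less harmful than smoking. Giving NRT users the full smoking odds ratio is therefore an upper bound. This also stands.

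Third, a reader might infer that NRT users among the controls corrupt the cotinine-outcome analysis. The article does not support that. A positive cotinine in such a woman is a true measurement of her nicotine exposure, whichever group she is in. The result only reflects mixed nicotine sources.

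Fourth, this is a condensed article. Drug history is collected at booking, women are asked about smoking and vaping status in a structured way, and confounders may enter the models. The full protocol or screening form may deal with NRT. That is possible, but the control rule is printed here and admits these women, so this is more than silence.

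Finally, an NRT exclusion does not remove women who stopped smoking unaided, who also qualify as controls. That is a real limit of the remedy.

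**Conclusion.** The point holds as a minor one. As written, the control definition admits women using only NRT into a group described as unexposed, and neither BCO nor any printed cotinine rule removes them. The consequence is probably small: under worst-case risk and an assumed 2% share, the wheeze odds ratio is 1.77 instead of 1.80, with about 78% power instead of 79%. If NRT carries no excess risk and these women have none left from earlier smoking, the outcome contrast is not biased at all.

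A reader might take the 10% scenario, with power near 70%, as the expected loss. The article does not support that: it gives no NRT share, and 10% would require nearly as many abstinent NRT users as current smokers. Nor does the rule for controls affect the vaper-smoker comparison. The figures rest on the assumed share, on full smoking-related risk among NRT users, and on the article's own baseline rates and test.

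**What to change.** Add to the control column of Table 1: no NRT or other nicotine product in this pregnancy. Bring the nomenclature note into line. Record NRT use in all groups so that it is available as a covariate. Repeat the vaper-control contrasts without controls whose third-trimester cotinine is above the assay's exposure cut-off; this would also remove controls with recent undisclosed vaping.

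Keep that last step as a sensitivity analysis. It selects on a measurement taken after enrolment, and cotinine does not identify the source of the nicotine. Women who stopped smoking unaided remain in the control group; the smoking history already taken at recruitment can be used to adjust for this.

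The cost is one screening question, one line in Table 1 and one extra analysis on data already being collected. A few otherwise eligible controls would be lost, from about 22,000 births a year when 400 are needed. If recruitment is well advanced, recording NRT use and running the sensitivity analysis are still possible.

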## Objectives

The ECHO study has four primary objectives described below:The primary obstetric objective is to establish whether infants born to women who vape are at a higher or lower risk of adverse outcomes in pregnancy compared to infants of combustible cigarette smokers and non-smokers.The primary neonatal objective is to assess anthropomorphic variation, if any, in newborn babies born to vapers in comparison to smokers and controls. The primary paediatric objective is to establish whether parent-reported and doctor-confirmed wheeze and/or asthma occurs more frequently in children exposed to vaping in utero compared with children of combustible cigarette smokers and non-smokers.The primary neurocognitive objective is to assess if there are significant differences in neurocognitive outcomes between the infants of a women who vape compared to infants of women who used combustible cigarette smokers and non-smokers.Globally, we aim to correlate, obstetric, neonatal, pulmonary, growth and neurocognitive differences, if any, to quantitative levels of cotinine excreted in maternal urine at in the third trimester.

### Proposed study design—PEOCT framework

A schematic of the study design is provided in Fig 1

**Fig. 1 Fig1:**
[figure not shown]
Study schematic

### Population

This prospective, multicentre, observational cohort will focus on women pregnant with a singleton fetus who self-report vaping, cigarette smoking, vaping and cigarettes smoking, or no exposure (controls). The obstetric portion of the study operates from three recruitment sites; The Coombe Hospital, The Rotunda Hospital, and the National Maternity Hospital—these standalone maternity units, based in Dublin, Ireland’s capital city, cumulatively deliver approximately 22,000 women annually [31–34].

Smoking and vaping patterns will be assessed using a combination of digital validated patient questionnaires administered at set timepoints throughout pregnancy, in addition to objective assessment of exhaled breath carbon monoxide (BCO) assessed by point of care exhaled carbon monoxide breathalysers (Bedfont’s ‘Smokerlyzer’® device) at each antenatal study visit. Nicotine levels will be assessed using quantitative urinary cotinine, analysed by Eurofins Biomnis enzyme immunoassay.

Women are recruited prior to 24-week gestation after being directly asked about smoking and vaping status in a structured fashion at their booking visit; if they fulfil the eligibility criteria, they are then invited to partake in the study as either a vaper, a smoker, a smoker/vaper or a control (Table 1.).

**Table 1 Tab1:** Exposure status

Vaper	Vaper/smoker	Smoker	Control
• Reports vape use • BCO ≤4 ppm	• Reports dual use • BCO ≥ 5 ppm	• Reports cigarette smoking • BCO ≥ 5 ppm	• Denies cigarette smoking or vaping • BCO ≤4 ppm

A BCO measurement of ≥ 5 parts per million (ppm) was selected to define active smoking, in keeping with Irish National Clinical Guidance. Selection of BCO ≥ 5 ppm as a cutoff confers a sensitivity of 0.9 and specificity of 0.92 [35]. This is an important consideration in accurately classifying both smokers and smoker/vapers in addition to self-reported exposure status.

After screening, demographic and biometric data points are gathered, and a series of questionnaires are administered digitally as per the schedule outlined below:

### Sequence of questionnaire timepoints

At recruitment to assess baseline cigarette smoking and vaping historyAfter 20 weeks/mid-trimesterThird trimesterAfter birthAged 6 monthsAged 1 yearAged 2 years

Self-administered, digital questionnaires, accessed on a smartphone, laptop or PC, are completed by participants without the presence of an interviewer; this may increase the validity of the reported exposure, hence the decision to prefer this method [36] when gathering data on frequency, duration and reasons for vaping. Questionnaires included validated instruments (Fagerstrom) to assess nicotine dependence in both cigarette smokers and vapers [37, 38]. Infants of study participants in exposure and control groups will be assessed at 12 and 24 months corrected for gestational age at birth.

